### Data Collection

#### GP EMR Data Collection

To measure the primary outcome (ie, referrals to hospitals), pediatric referral data will be routinely collected from the GP EMRs via GRHANITE. This software will be remotely embedded into all participating GP medical software computers (compatible with BP or MD EMR software). For research purposes, GP data will be collected on all patients younger than 18 years. These data will be deidentified at the patient level, although the identity of the GP will be supplied to the research team. Collection of GP EMR referral data will commence for all practices following randomization and will continue for the duration of the trial.

The ability to record referral information, manage deidentification and consent processes, is a principal rationale for the use of the GRHANITE technologies and was demonstrated to be acceptable to GPs in the SC4C study [19].

#### GP Referrals

Data on GP referrals is not recorded in a standardized fashion in the GP EMR. Therefore, in order to measure the primary outcome, that is, referrals to hospitals, the GRHANITE team developed a tailored referral pop-up window (Section S5 in Multimedia Appendix 3) of common referral options to be completed by GPs following each pediatric consultation. This specific software extracts information regarding whether the GP referred a child and where (eg, no referral, hospital OP, or emergency department, private pediatrician, or allied health). The research team will continuously monitor GP data to promptly identify and address any technical issues posing a risk to data acquisition.

#### GP Quality of Care

GRHANITE will be used to extract deidentified patient-level data routinely collected on all patients younger than 18 years seen by consented GPs throughout the trial. Deidentified pediatric patient data will be limited to patient demographics, reason for visit, diagnoses, referrals, prescriptions, ordered imaging and pathology testing, and Medicare item billing. The patient-level data will be used to characterize GP pediatric visits (eg, number of children seen, gender of the children, and common diagnoses) and compare quality of care for common conditions before and after the model of care is implemented, based on the CareTrack Kids indicators [28].

A natural language processing algorithm, developed by the Computing and Information Systems at the UoM for the SC4C trial, will be used to automatically transform GP EMR clinical free text of “reason for visit” or diagnosis into structured clinical data, based on the Systematized Nomenclature of Medicine Clinical Terminology [29].

#### GP Model of Care Engagements

As per our ethics approval, GP engagement with the components of pediatric support, such as coconsults, case discussion, phone/email, and SCHP access, will be recorded by the following processes and stored on the secure UNSW network drive. For coconsults, GPs will record deidentified patient information (age, gender, presenting problem, and reason for coconsult) via the SCHN Microsoft Bookings. For email, phone, and case discussions, pediatricians will record via REDCap each engagement, including GP name and deidentified patient information on the topic or concern discussed. For SCHP usage, the SCHP team will record the GP name and track GP access with the SCHP learning platform.

#### GP and Family Data Collection

GP and family survey data collection will occur preintervention (baseline) and in the last month of the SUSTAIN model of care (intervention) for each practice.

A web-based GP Survey (Section S3 in Multimedia Appendix 4) will be used to measure GP experience and confidence in pediatric care, completed by all participating GPs via REDCap. Based on the SC4C trial, the survey collects information including GP demographics, factors that impact their decision to refer a pediatric patient, and knowledge and confidence in pediatric care and services. GP name and general practice will be recorded for survey completion tracking, but will not be attached to the survey responses.

A web-based family survey (Section S4 in Multimedia Appendix 2) will be used to measure caregivers’ perceptions and experience of pediatric care provided at their general practice. To provide data on a “whole of practice” level, caregivers of a patient <18 years, regardless of whether they attended a consultation with a participating GP, will be eligible to complete the Family Survey via REDCap. The survey collects information on the child/family regarding a GP visit up to 3 months prior. These surveys are voluntary, and responses are anonymous.

No power calculation has been performed, as we will recruit as many families as possible during this timeframe and use all available data.

SUSTAIN GP and family surveys have been adapted from the SC4C study and comprise items generated by the SC4C investigators and drawn from previously published literature [19,30,31]. Data collection timepoints for participant enrollment and interventions can be found in Table 2.

**Table 2. T2:** Outline of participant enrollment, intervention, and data collection timepoints.

	Enrollment (–t_1_)	Allocation (t_0_)	Study period			Close out (t_x_)
			Control period (t_1_)	1-month Embedding period (t_2_)	11-month Intervention period (t_3_)	
Enrollment						
General practice eligibility screen	✓					
Informed GP^a^ consent	✓					
General practice intervention allocation		✓				
Intervention						
Virtual GP-pediatrician coconsultation				✓^b^	✓	
Virtual case discussions				✓^b^	✓	
Pediatrician phone/email support				✓^b^	✓	
GP access to SCHP^c^				✓^b^	✓	
Primary outcome						
GP referral outcomes						
GRHANITE extracted from routinely collected GP EMR^d^ data			✓	✓^b^	✓	
Secondary outcomes						
GPs						
Quality of care						
GRHANITE EMR data extraction on care quality based on measurement of the CareTrack Kids indicators: asthma, bronchiolitis, constipation, upper respiratory tract infections, and infant crying and gastroesophageal reflux			✓	✓^b^	✓	
Baseline and intervention /follow-up surveys						
GP demographics			✓		✓	
Confidence in pediatric care and access to pediatric services			✓		✓	
Skills to manage child health			✓		✓	
Awareness and use of HealthPathways			✓		✓	
Model feasibility, acceptability, feedback, and patient benefit					✓	
Families/caregivers						
Baseline and intervention /follow-up surveys						
Family demographics			✓		✓	
Confidence in GP care			✓		✓	
Quality of care and interactions with the GP			✓		✓	
Preference for pediatrician referral and GP review			✓		✓	
General practice implementation focus groups				✓		
Implementation evaluation						✓
Economic evaluation						✓
Reporting and manuscript reporting						✓

a GP: general practitioner.

b Data collected during the embedding period will not be analyzed.

c SCHP: Sydney Child Health Program.

d EMR: electronic medical record.

### Sample Size Calculation

In the SC4C pilot study, there was a 7% reduction in GP referrals to hospital EDs and OPs, but we have powered our trial using a conservative 4% reduction [19,32]. The sample size of 18 practices with at least 60 pediatric consultations per practice per month will have 90% power to detect a 3.7% reduction (from the baseline rate of 10%) in the percentage of children who are referred to OP clinics or EDs following their GP appointment, assuming an intracluster correlation of 0.06 (derived from the pilot data [19]) and 2-sided type I error of 0.05. With the same sample size, we will have 80% power to detect a 5.5%‐6.55% reduction in the proportion of referrals to OP or ED for our planned stratification analysis by practice rurality, GP baseline referring level, years of practice, and gender.

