### Statistical Analysis

We will undertake descriptive analysis to describe the GP referral rate alongside the numbers of all children seen and the numbers of children referred to OP or ED by month during the study period for each practice.

All available data from each recruited GP and family will be analyzed according to an intention-to-treat principle. For the outcomes of GP referrals identified using the GP EMR data (eg, GP referral to OP clinic or ED), we will conduct mixed effects logistic regression, fitted to data collected during the control and intervention periods. The model will include a fixed effect of group (intervention vs control) and adjust for calendar time (as a continuous variable), and random effects to allow for variation in the outcomes for 3 hierarchical levels, including GP practice, GP within each practice, and patients seen by each GP.

Secondary outcomes collected at the child consultation level will be analyzed similarly, with separate models for the 5 common childhood conditions to measure quality of care. GP survey outcomes will be analyzed using mixed effects logistic regression, again including a fixed effect for group by intervention status and calendar time, and a random effect for GP practice, GPs, and patients.

We will control for baseline levels of GP referral for each practice in the analyses, GP-level factors (eg, rurality of the practice’s location, billing type, GP gender, years of practice, and number of children patients seen per week), and patient-level sociodemographic factors (eg, age at the encounter and socioeconomic status of residence). We will also consider whether the intervention effect varies by rurality of practice and GP-level factors (eg, referring level during baseline, years of practice, and GP gender) by the inclusion of interaction terms between group (intervention vs control) and these variables in the regression models.

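### A single detectable fall of 5.5–6.55 points is claimed for strata of GP baseline referring level, but strata cut on the baseline rate cannot all start at the overall 10%

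*Protocol article*

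**What the plan says.** All the power inputs are in the protocol article, Sample Size Calculation. The design has a "sample size of 18 practices with at least 60 pediatric consultations per practice per month" and "will have 90% power to detect a 3.7% reduction" from a 10% baseline, "assuming an intracluster correlation of 0.06 (derived from the pilot data" and with a "2-sided type I error of 0.05". The same sample is then said to give 80% power for a fall of 5.5–6.55% in the "reduction in the proportion of referrals to OP or ED for our planned stratification analysis by practice rurality, GP baseline referring level"; GP gender and length of practice complete the list.

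No baseline rate, cut-point or size is given for any stratum, and the two ends of the range are not assigned to stratifiers. The scale of the intracluster correlation is not stated either.

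The Statistical Analysis section plans interaction terms between group and practice rurality and "GP-level factors (eg, referring level during baseline, years of practice, and GP gender" in a mixed effects logistic model, so effect variation by referring level is to be examined.

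**The concern.** Strata by rurality, GP gender or years of practice could each start near 10%. Strata by baseline referring level differ on the baseline rate by construction, so one lies below 10% and the other above it. If the low stratum starts well below 10%, an absolute fall of 5.5–6.55 points may equal or exceed everything that stratum has to lose. A power statement for such an effect tells the reader nothing about that stratum. A reader could also take a null result among low referrers as adequately powered on the strength of this sentence.

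**Working it through.** **Inputs from the article.** Mean rate 10%, intracluster correlation ρ = 0.06, 18 practices, 60 consultations per practice-month, two-sided α = 0.05 (Sample Size Calculation). Three practices switch each month, so 6 steps; one embedding month is excluded, followed by 11 intervention months (Trial Design). Data run from September 2023 to February 2025, 18 months (Results).

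**Step 1: reproduce the main figure.** Stepped-wedge generalised least squares (Hussey–Hughes) with month effects:
- V = (1−ρ)s²/m·I + ρs²·J for each practice, with s² the average of p₀(1−p₀) and p₁(1−p₁) and m = 60.
- SE² is the treatment element of (ΣX′V⁻¹X)⁻¹.
- Power = Φ(d/SE − 1.96).

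For 10% to 6.3% this gives 91%. A 7-period version without the embedding month and with variance at 10% gives 88%. Both are close to the stated 90%; other variants run from 71% to 99%.

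**Step 2: absolute or relative?** A 5.5–6.55% relative fall from 10% is 0.55–0.655 points. In the 18-month model, power for this is about 7–8% even with the full sample. The range must be absolute points, as the 3.7% is.

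**Step 3: where the range comes from.** Keeping the 10% baseline, the 80% detectable fall is 4.2–5.9 points with half the sample and about 5.0–7.2 points with a third, across model variants with categorical time. The stated 5.5–6.55 fits a common 10% start.

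**Step 4: implied stratum baselines (assumption: median split).** On the proportion scale, the between-unit SD is √(0.06 × 0.10 × 0.90) = 7.3 points. The article's one correlation is applied here to the units being split.

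| Reading | Low half | High half |
|---|---|---|
| Beta(1.567, 14.1): mean 0.10, ρ = 0.06 | 4.4% | 15.6% |
| Logit-normal, SD 0.8 (ρ ≈ 0.06 on the proportion scale) | 4.8% | 15.2% |
| ρ on the latent logit scale: SD = √(0.06/0.94 × π²/3) = 0.46 | 6.8% | 13.2% |
| Beta, units classed on 60 / 30 / 10 visits | 5.1 / 5.5 / 6.6% | 15.0 / 14.5 / 13.4% |

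The last row matters because the inclusion criteria ask for only 2 weeks of control referral data per GP.

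**Step 5: the stated fall as a share of the low stratum's referrals.**

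| Low baseline | 5.5 points | 6.55 points |
|---|---|---|
| 4.4% | 5.5/4.4 = 125% | 6.55/4.4 = 149% |
| 4.8% | 115% | 136% |
| 5.5% | 100% | 119% |
| 6.8% | 81% | 96% |

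**Step 6: detectable falls from stratum baselines.** This uses the 18-month model of step 1 with m = 30 per stratum, ρ kept at 0.06 and 80% power. OR = [p₁/(1−p₁)]/[p₀/(1−p₀)].

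| Baseline | Detectable fall | Share of baseline | OR |
|---|---|---|---|
| 4.4% | 2.8 points | 63% | 0.36 |
| 4.8% | 2.9 points | 60% | 0.39 |
| 6.8% | 3.5 points | 52% | 0.47 |
| 13.2% | 5.0 points | 38% | 0.59 |
| 15.6% | 5.4 points | 35% | 0.62 |

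Other design variants with half the sample and a 4–6% baseline give about 3.0–4.6 points.

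**The case against.** The strongest reply is that power is not overclaimed. From 10%, a fall to 4.5% or 3.45% is an odds ratio of (0.045/0.955)/(0.10/0.90) = 0.42 or (0.0345/0.9655)/(0.10/0.90) = 0.32. The illustrative low-stratum odds ratios, 0.36–0.47, lie in or near that range, and the high-stratum ones, about 0.6, are closer to 1. On the scale of the planned logistic model the claim is therefore about right for low referrers and cautious for high referrers. This stands. A reader might infer that the trial is underpowered in these strata, or that a corrected figure would look worse. It would not: the detectable absolute falls become smaller.

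It is also fair that the article gives no rate for low referrers. A reader might take 4–6% as a known starting rate, or conclude that the stated fall is impossible under any split. Neither is supported. The rate depends on the assumed distribution, the scale of the correlation, the cut-point and the amount of baseline data. At 6.8%, both ends of the range are arithmetically possible, though they would remove 81% and 96% of referrals. A fall of 5.5 points is strictly impossible only when the baseline is below 5.5%.

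Finally, using a common 10% for subgroup planning is a familiar simplification, and inputs can be left to a fuller document. That covers the missing detail. It does not cover quoting one absolute figure for strata that differ on the baseline rate by definition. Nor does any passage tie a decision to a null result in a stratum, so the risk of misreading is a risk only.

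**Conclusion.** The point holds for one of the four stratifiers. The 5.5–6.55 point range fits a common 10% baseline, and strata of GP baseline referring level cannot share one. With a median split, mean 10% and correlation 0.06, low referrers start at about 4.4–4.8%, or up to about 6.8% if the correlation is on the latent scale or GPs are classed on few visits. High referrers start at about 13–16%. The stated fall would then remove roughly 80% to more than 100% of low referrers' referrals, so it has no usable meaning for them, and one absolute figure cannot serve both strata.

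The defect is an unattainable absolute effect, not a lack of power. The primary sample size, and the figure as applied to rurality, years of practice and gender, are not affected by this argument. The stratum rates are assumptions and should be shown as such.

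**What to change.** In Sample Size Calculation, remove GP baseline referring level from the sentence with the 5.5–6.55% range. Add a sentence giving detectable effects separately for low and high referrers, each from its own assumed baseline rate, with the cut-point, the scale of the correlation and the range of baselines stated. Odds ratios are preferable, to match the logistic model in Statistical Analysis.

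As an illustration, with half the visits in each stratum and month effects, the detectable fall is about 2.8–3.5 points for low referrers and about 5.4 points for high referrers (about 5.0 if they start at 13.2%). The sponsor should replace these with values from its own pilot rates.

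The text should not assert that low referrers cannot show a 5.5 point fall, since that depends on the assumptions. The cost is wording and a short recalculation, with no change to conduct or sample size.

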### Engagement/Retention Strategies

Several methods will be used to maintain general practice and GP engagement in the trial and minimize “withdrawals” or “lost to follow-up.” These will include email reminders on accessing the SUSTAIN model of care components, “touch point” meetings by the researchers with practices, and quarterly newsletters providing updates and relevant trial information.

### Statistical Analysis

We will undertake descriptive analysis to describe the GP referral rate alongside the numbers of all children seen and the numbers of children referred to OP or ED by month during the study period for each practice.

All available data from each recruited GP and family will be analyzed according to an intention-to-treat principle. For the outcomes of GP referrals identified using the GP EMR data (eg, GP referral to OP clinic or ED), we will conduct mixed effects logistic regression, fitted to data collected during the control and intervention periods. The model will include a fixed effect of group (intervention vs control) and adjust for calendar time (as a continuous variable), and random effects to allow for variation in the outcomes for 3 hierarchical levels, including GP practice, GP within each practice, and patients seen by each GP.

Secondary outcomes collected at the child consultation level will be analyzed similarly, with separate models for the 5 common childhood conditions to measure quality of care. GP survey outcomes will be analyzed using mixed effects logistic regression, again including a fixed effect for group by intervention status and calendar time, and a random effect for GP practice, GPs, and patients.

We will control for baseline levels of GP referral for each practice in the analyses, GP-level factors (eg, rurality of the practice’s location, billing type, GP gender, years of practice, and number of children patients seen per week), and patient-level sociodemographic factors (eg, age at the encounter and socioeconomic status of residence). We will also consider whether the intervention effect varies by rurality of practice and GP-level factors (eg, referring level during baseline, years of practice, and GP gender) by the inclusion of interaction terms between group (intervention vs control) and these variables in the regression models.

We will assess whether the correlation structure has been mis-specified. The primary analysis will assume an exchangeable within-cluster correlation structure, meaning that the correlation between any 2 individuals within the same cluster is considered constant. To evaluate the impact of potential misspecification, we will conduct a sensitivity analysis using a block-exchangeable correlation structure within periods. This structure assumes stronger correlations among individuals within the same period, with weaker correlations across different periods. To implement this, we will extend the random-effects model to include an interaction between time and the GP practice random effect.

Prior to analysis, we will understand the mechanisms of the occurrence of missing data in the primary and secondary outcomes. If there is a small number of missing data (<5%), complete case analysis will be presented as the primary analysis. Missing data can occur due to 2 main reasons, considering the current study design: the pop-up failure to launch due to technical issues (nonmonotone missingness), and GP or GP practices withdrawal from the trial (generally monotone missingness, though could also be instances of nonmonotone, for example, personal leave such as maternity leave and retirement). It is reasonable to assume that data missing due to technical failure or personal leave occur missing completely at random. Based on our knowledge, the main reason for GP and GP practice withdrawal is the GP leaving the participating practice. Therefore, it is reasonable to assume these missing data occur as missing at random, and we will undertake multiple imputation to account for the impact of the missing data on the outcomes. It is unlikely that data is “missing not at random (MNAR)” in the nature of this current study, that is, GPs withdraw from the study because of their referral patterns, and this cannot be accounted for by all observed data. If we identify any MNAR, we will not impute the data and will report and discuss the results with limitations and the reasons potentially responsible for the missingness.

We will conduct an intention-to-treat analysis as the primary approach to understand the effect of offering the intervention on referral patterns, under real-world conditions. This means the data will be analyzed based on the information generated from a consenting GP in a randomized GP practice, according to the intervention that is supposed to be delivered in a particular period, irrespective of whether the intervention has been implemented as planned (practices analyzed by randomized step, irrespective of actual start date). Prespecified sensitivity analyses included as-treated and per-protocol analyses, modeling approaches that incorporate the exact calendar date of intervention initiation (to address early or delayed starts), and methods to explore the influence of contamination or noncompliance (for example, complier average causal effect estimates or instrumental variable techniques where appropriate).

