**Figure 1. F1:**

Stepped wedge randomized control trial design.

Each general practice provides control period data (referral and medical record data) during the control period (standard GP care, no SUSTAIN model operating). Each month thereafter, 3 practices switch concurrently from control to intervention where a pediatrician supports GPs through telehealth coconsultations, virtual case-based discussions, and being available by phone and email contact in working hours. During the first month of the intervention for each practice, a 1-month transition period is allowed to embed the SUSTAIN model of care into the practice, where data do not contribute to the analysis. This embedding period assists with implementation of the model of care into the practice and allows time to address any procedural issues. After the embedding period, each practice is exposed to an 11-month intervention period. Sustainability data are collected following cessation of the intervention until the intervention is completed for the final practice.

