There are minimal anticipated risks to patient care, as opposed to the potential benefits, with this integrated GP-pediatrician model of care proposed. However, since the model relies on relationship development between the pediatricians and GPs, it is feasible that personality issues may surface with potential negative consequences to the strengthening of confidence and skills that this model aims to enhance in primary care providers. The use of telehealth and virtual modalities for the development of these relationships may also be a challenge, as opposed to in-person models. These difficulties will be explored particularly through the implementation evaluation, where GPs, practice staff, and pediatricians are involved in focus group discussions or interviews to uncover these underlying issues. Using digital tools for health and education delivery has become more technologically stable and acceptable since the COVID-19 pandemic, and in-person modalities are less affordable and scalable. Although the estimated time available for the pediatrician to provide support for the GPs is based on prior projects, it is conceivable that this is under or overestimated. If underestimated, GPs may find it difficult to obtain the support required to assist with behavior change in practice. If overestimated, this could have financial implications for underused specialist time. These issues will be evaluated carefully, both quantitatively and qualitatively, as well as through the economic evaluation, to determine the most cost-effective way of delivering the intervention. The voice of consumers (patients/families) is obtained through anonymized surveys at baseline and postintervention, with an invitation to patients/families to voluntarily participate in an interview to gather their views on pediatric care provided at GP practices that have participated in the SUSTAIN trial.

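### The single constant intervention effect weights early exposure months heavily and late ones negatively, so a gradual build-up could be underestimated, and no listed analysis would show it

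*Protocol article*

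**What the plan says.** The Statistical Analysis section fixes the primary model as a mixed effects logistic regression, "fitted to data collected during the control and intervention periods". It contains "a fixed effect of group (intervention vs control") and is to "adjust for calendar time (as a continuous variable"). On correlation, the same section says: "The primary analysis will assume an exchangeable within-cluster correlation structure".

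The design text beside Figure 1 has three practices switching each month. The first month of each practice is set aside for embedding and left out of the analysis. "After the embedding period, each practice is exposed to an 11-month intervention period". The Results section dates the layout: data collection from September 2023 to February 2025, first practices starting in October 2023, last practices finishing at the end of February 2025.

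The planned interactions are with rurality and GP characteristics. The planned checks are a block-exchangeable correlation structure and the set introduced by "Prespecified sensitivity analyses included as-treated and per-protocol analyses", which goes on to exact start dates and to contamination or noncompliance. None of these lets the effect depend on how long a practice has been exposed.

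**The concern.** One constant term assumes that the full effect is present in the first analysed month and stays level for 11 months. The intervention combines shared consultations, case discussions and a learning platform, and the Discussion accepts that its success depends on working relationships ("since the model relies on relationship development between the pediatricians and GPs") and on GPs changing their behaviour. Both may take time.

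In a stepped wedge design, a constant-effect model fitted to an effect that varies with exposure time does not in general return the average of that effect. The departure is large here because all 18 practices cross over within six months and are then followed, exposed, for up to a year with no controls left. The cost per referral avoided in the Economic Evaluation section is to be aligned with this analysis, so a distorted estimate would carry into it.

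**Working it through.** **Inputs.** The Sample Size Calculation section gives "The sample size of 18 practices with at least 60 pediatric consultations per practice per month", an ICC of 0.06, a baseline referral rate of 10%, a 3.7-point reduction, two-sided alpha of 0.05 and 90% power. With three practices per month there are six sequences, starting October 2023 to March 2024. Each has 1 to 6 control months, one dropped month and 11 analysed months.

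- Control practice-months: 3 × (1+2+3+4+5+6) = 63.
- Analysed exposed practice-months: 18 × 11 = 198.
- The last control month is February 2024. Exposed practice-months up to then are 12, 9, 6 and 3 in analysed months 1, 2, 3 and 4, so 30 of 198 (15%), and none in months 5 to 11.

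**Stated power.** Variances use 0.10 × 0.90 = 0.09. The between-practice variance is 0.06 × 0.09 = 0.0054, and the variance of a practice-month mean within practice is 0.94 × 0.09 / 60 = 0.00141. A classic seven-period, six-step layout with period effects gives 88.4% power. The documented 18-month layout with month effects, and the variance taken at the mean rate of 8.15%, gives 91.2%. Both agree with the stated 90%. The same layout with the planned linear time gives 98.6% to 99.5%. All of these assume a constant effect.

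**Weights.** The generalised least squares estimate of the group effect is the first element of (D'V⁻¹D)⁻¹D'V⁻¹y. Summing its coefficients over the cells at analysed month e gives a weight w(e), and the expected estimate is Σ w(e)·δ(e), where δ(e) is the true effect in that month.

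| Analysed month | 1 | 2 | 3 | 4 | 5 | 6 | 7 | 8 | 9 | 10 | 11 |
|---|---|---|---|---|---|---|---|---|---|---|---|
| Linear time | 0.45 | 0.38 | 0.31 | 0.24 | 0.16 | 0.09 | 0.02 | -0.05 | -0.13 | -0.20 | -0.27 |

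The weights sum to 1, so a constant effect is recovered without bias. With month effects in place of linear time they run from +0.65 to -0.14.

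**Build-up curves (assumed).** The effect rises linearly to -3.7 points. When the build-up starts in the embedding month, analysed month 1 is the second month of exposure. The standard error of the constant effect is 0.89 points, and power is Φ(|estimate|/0.89 - 1.96) for an estimate in the right direction.

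Example, full by month 4: the fractions of full effect are 0.5, 0.75, then 1.
- True mean: (0.5 + 0.75 + 9)/11 = 0.93, so -3.5 points.
- Estimate: 1 - 0.5 × 0.45 - 0.25 × 0.38 = 0.68, so -2.5 points.
- Power: Φ(2.5/0.89 - 1.96) ≈ 80%.

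| Build-up, linear time | True 11-month mean | Expected estimate | Power |
|---|---|---|---|
| From embedding, full by month 3 | -3.6 | -3.1 | 94% |
| From embedding, full by month 4 | -3.5 | -2.5 | 80% |
| From embedding, full by month 6 | -3.1 | -1.4 | 33% |
| From embedding, full by month 12 | -2.2 | +0.3 | about 1% |
| After embedding, full by analysed month 4 | -3.2 | -1.5 | 37% |

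With month effects, the month-12 case gives an estimate of about zero. An effect that is full in analysed month 1 and wanes linearly to zero in month 11 has a true mean of -1.85 and an estimate of -4.8, which is 2.6 times too large.

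**Robustness.** These are risk-difference calculations with a practice random effect only. A logistic check of the month-12 case gave a fitted odds ratio of 1.04 against a true average of 0.75. With linear time, that case returns -4% to -8% of the full effect for ICCs of 0.005 to 0.06, and -8% for cluster autocorrelations of 0.8 to 1.0. The planned block-exchangeable analysis would therefore not reveal the problem.

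**The case against.** The strongest objection is that no section says the effect grows over the year. The Discussion names relationships and behaviour change but gives no time course, and a shared consultation or a phone call can alter the referral of the child being seen at once. The dropped month is itself an allowance for build-up: Table 2 shows all four components delivered in it. This stands. It is why the main figures above count that month as exposure, and why a build-up complete by month 3 costs little (-3.1 against -3.6).

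A reader might go further and infer that an effective programme would be reported as ineffective or harmful. The documents do not support that. A reversed sign needs a build-up over most of the year or a long delay, and +0.3 with a standard error of 0.89 would not be taken as evidence of harm.

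It can also be said that extra sensitivity analyses belong in an analysis plan that is not shown, and that the monthly referral rates planned for each practice give a descriptive view of build-up. An unseen plan may contain such a model. But this article fixes the primary model and names its prespecified sensitivity analyses, and monthly rates alone do not separate exposure time from calendar trend.

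Finally, an exposure-time model is imprecise, and could be used to rescue a null result. That also stands, and limits what should be asked for.

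**Conclusion.** The point holds as a weakness in the planned set of analyses. The constant-effect estimate is dominated by the first few analysed months, counts months 8 to 11 negatively under linear time, and is an 11-month average only if the effect does not change with exposure. Under a build-up starting in the embedding month, the expected estimate is about 88% of the true mean if complete by month 3 (3.14/3.59), 73% by month 4 (2.51/3.45) and 43% by month 6 (1.35/3.14). A later start to the build-up makes the loss larger, and waning produces overstatement.

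The weights follow from the documented layout and the stated ICC and consultation numbers. The shapes of the curves are assumptions. The primary model is not invalid, and the finding gives no licence to read a null result as a hidden benefit.

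**What to change.** Keep the primary model. Add to the prespecified sensitivity analyses in the Statistical Analysis section a model in which the effect depends on months since start, using exposure-time categories or a random exposure-time effect. Report the average effect over analysed months 1-4, the only ones with concurrent controls, and over months 1-11, side by side with the constant-effect estimate. State that the constant-effect estimate mainly reflects early exposure. Attach no rule for discounting a null primary result.

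The cost is one extra model with imprecise averages. With linear time the standard errors are about 1.7 points for months 1-4 and 2.7 for months 1-11, against 0.9 for the constant effect. With month effects they are about 1.8 and 3.0, against 1.2. The 11-month average from a model with a separate effect for each exposure month would have only about 27% to 31% power for 3.7 points with linear time. That is why it belongs beside the primary model and not in its place.
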